### 9.1.1.4. Follow-Up of Adverse Events

All AEs will be followed until resolution, until the condition stabilizes, or until the subject is lost to follow-up. The investigator will ensure that follow-up includes any supplemental investigations that may be indicated to determine the nature and/or causality of the AE or SAE. The sponsor may require that the investigator perform or arrange for the conduct of additional investigations (not otherwise required per protocol) to determine the nature and/or causality of the AE or SAE.

Any subject that becomes pregnant during the study must be followed up to delivery.

### 9.1.2. Submission of Serious Adverse Event Reports

When an SAE occurs, it is the responsibility of the investigator to review all documentation (e.g., hospital progress notes, diagnostic reports, laboratory assessments) relative to the event. The investigator will then be responsible for recording all relevant information on the appropriate AE CRF and SAE form. New information or corrected information will be recorded on a follow-up SAE report.

Any SAE that occurs at any time between the signing of the informed consent and 30 days after the last dose of study medication, regardless of the relationship to study medication, must be reported on the SAE CRF, and a copy of this form must be faxed to the drug safety manager, and in Argentina to ACTIVA-CRO, at the fax number(s) listed below within 24 hours of knowledge of the event:

### 9.1.3. Regulatory Reporting Requirements for Serious Adverse Events

The sponsor has a legal responsibility to notify, as appropriate, regulatory authorities about the safety of a product under clinical investigation. Prompt reporting of SAEs by the investigator to the drug safety manager is essential so that legal and ethical requirements for the safety of other subjects are met. The drug safety manager will be responsible for reporting all SAEs to the sponsor and to the FDA; the sponsor will be responsible for reporting SAEs to the European regulatory authorities. The sponsor and/or designee (e.g., CRO) will report SAEs to other pertinent regulatory authorities (i.e., in India and Argentina) as indicated in the figure below.

[figure not shown]

Details of the reporting procedures for SAEs are outlined in the SAE Management Plan designed for this study by the CRO.

The investigator will comply with local requirements related to the reporting of SAEs, safety notifications, and other safety information related to the trial to their local IRB/IEC. Reporting of safety information will be according to ICH/GCP guidelines and will follow requirements of the countries in which study sites are located.

#### **9.1.3.1. Regulatory Reporting Requirements for SUSARS**

All elements required by the European Union for reporting suspected unexpected serious adverse reactions (SUSARs) are in the Study Manual. Reporting will be according to ICH/GCP guidelines and will follow requirements of countries in which study sites are located.

### **9.2. Vital Signs**

Vital sign values will be obtained as detailed in Section 5.3.1.2. Any clinically significant changes in vital signs will be reported as AEs as described in Section 9.1.1.2. Clinically significant hypotension (i.e., a  $\geq 30$  mmHg drop in systolic blood pressure accompanied by clinical findings/symptoms, or a systolic blood pressure of  $\leq 70$  mmHg) and/or anaphylactic reactions (significant hypotension with generalized hives/angioedema or bronchospasm) warrant discontinuation of the infusion and administration of appropriate supportive care as deemed necessary by the investigator (may include epinephrine, antihistamine, corticosteroids, supplemental oxygen, expansion of the plasma volume as necessary, etc.). These occurrences must be recorded in the CRF as AEs. At the discretion of the investigator, the subject may be withdrawn from the study, but will complete the follow-up visits. Before listing changes in vital signs as AEs, each change should be assessed for clinical relevance.

### **9.3. Clinical Laboratory Tests and Direct Coombs' Test**

#### **9.3.1. Clinical Laboratory Tests**

Blood should be drawn according to the procedures outlined in the Laboratory Manual provided to each investigative site by the central laboratory. The volume of blood for each sample per study visit is in Table 1.

On Day 1 of each infusion and visit(s) to check platelet count (if applicable), the subject's platelet count will also be done locally.

Additionally, for those subjects screened more than 14 days prior to Day 1 of the first infusion, a blood sample for assessment by the local laboratory must be taken to assess CBC, LFTs, serum Creatinine/BUN prior to enrolment in the study.

Blood samples will be drawn at scheduled times for the following laboratory determinations:

| Laboratory A:                                                                                                                                                                                                                                                                                                                                                                                                                                                                                          | Laboratory B:                                                                                                                    |
|--------------------------------------------------------------------------------------------------------------------------------------------------------------------------------------------------------------------------------------------------------------------------------------------------------------------------------------------------------------------------------------------------------------------------------------------------------------------------------------------------------|----------------------------------------------------------------------------------------------------------------------------------|
| 
 
• CBC with differential 
 
○ WBC
 
○ RBC
 
○ Hematocrit
 
○ Hemoglobin
 
○ Platelet Count
 
○ Neutrophil %
 
○ Lymphocyte %
 
○ Eosinophil %
 
○ Monocyte %
 
○ Absolute Neutrophil
 
○ Absolute Lymphocyte
 
○ Absolute Eosinophil
 
○ Absolute Basophil
 
○ Absolute Monocyte
 
 
 
• Platelet count
 
 | 
 
• Bilirubin
 
• Creatinine
 
• BUN
 
• ALT
 
• AST
 
 |

In addition, the following will be done:

- NAT for HCV, HIV and Parvovirus B19
- Serology for HIV1 and HIV2, HCV, HBsAg.

If a positive result on an NAT or serologic test occurs, it will be repeated at the subject's next scheduled visit.

- IgG, IgA and IgM will be monitored at the End of Study visit and compared with the values obtained at screening. In addition, IgG will be monitored pre-infusion on Days 1 and 2 and at the study visits on Days 3, 5, 9, 14, 21 and 32, for the first course of GAMMAPLEX only.
- Reserve sample. A 5-mL blood sample (minimum 1 mL serum) will be obtained on each occasion that Laboratory A samples are taken and will be stored at -70°C at the central laboratory in the event that repeat tests are required. These samples will be discarded at completion of the study.
- Retention sample. In order to comply with the European CPMP requirements [22], a 2.5-mL blood sample will be collected from each subject immediately before the first infusion and at the End of Study visit. Serum (1 mL) will be stored in 2-mL tubes at -70°C for 15 years. These serum samples will be stored at a central archive (Cryo-Store).

Samples will be used for serology and NAT testing if required in the future. The central laboratory will coordinate the handling and shipping of these samples.

- Urinalysis

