### 5.3. Study Visits

The study visits are summarized in the study flow chart (Figure 1). The schedule of assessments is in Table 1, and in Table 2 for subjects who receive additional treatment courses. The study visits are identified as follows:

- Screening visit (can occur up to 6 months prior to Day 1)
- Visit(s) to check platelet count, (if applicable) – for those subjects whose platelet count is above  $20 \times 10^9/L$  at the screening visit, samples can be sent to the local laboratory to check the platelet count. For subjects screened more than 14 days prior to Day 1, additional safety laboratory samples will be analyzed by the local laboratory e.g. CBC, LFTs, serum Creatinine/BUN.
- First course of GAMMAPLEX – there will be 2 infusion visits on consecutive days (Days 1 and 2)
- Follow-up – 6 follow-up visits from Day 3 to Day 32
- Second and third courses of GAMMAPLEX – at the discretion of the investigator, subjects may receive 1 or 2 more courses of GAMMAPLEX within the period 32 to 90 days following the first course of GAMMAPLEX. Each course will consist of 2 infusions on consecutive days and will be scheduled at an appropriate time following the first treatment course, depending upon the subject's response to the previous treatment course of GAMMAPLEX
- End of Study visit – For all subjects this visit will be approximately 3 months after the first infusion of the last course of GAMMAPLEX and will be the End of Study visit for all subjects irrespective of whether they received 1, 2, or 3 courses. For subjects receiving 1 treatment course of GAMMAPLEX only, this visit will take place on Day 90.

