### **5.3.1. Description of Study Visits**

#### **5.3.1.1. Screening Visit**

##### *Subject Eligibility*

The subject's eligibility to participate in the study will be assessed at this visit according to the inclusion and exclusion criteria. This visit can occur up to 6 months prior to Day 1.

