##### *Complete Medical History*

A complete medical history will be obtained from each subject at this visit. The history will specifically include documentation of the diagnosis of chronic ITP, the reason why other causes of thrombocytopenia were excluded, general medical history, history and outcome of previous use of and/or reactions to any IGIV or other blood product, history and treatment of ITP, and history of bleeding/hemorrhage. Bone marrow examination is not required, but if it has been done, it should be consistent with ITP with, for example, normal or increased megakaryocytes. For subjects who have had bone marrow examinations, the date and findings should be recorded on the Case Report Form (CRF) at the time of screening.

The medical history must include the use of previous IGIV treatments received; the product name, the unit dose, and how they were tolerated must be recorded. The previous use of an IGIV product must be documented in the subject's CRF. In addition the treatment regimen and dose of corticosteroids, azathioprine, cyclophosphamide, and attenuated androgens must be documented in the subject's CRF.

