##### *Vital Signs*

Vital signs assessed by qualified personnel will be entered on the CRF. The vital signs to be observed will be diastolic and systolic blood pressure (mmHg), pulse rate (beats/min), respiration rate (breaths/min), and oral temperature (°C). The subject must be in the same position each time vital signs are obtained. The vital signs are also a safety variable (see Section 9.2.).

*Blood Samples for Laboratory Tests*

Blood samples will be obtained for Laboratory A and Laboratory B (Clinical Laboratory tests are a safety variable, see Section 9.3). If a subject is otherwise eligible, but the platelet count is greater than  $20 \times 10^9/L$ , the subject will not be enrolled. If at a subsequent visit (within 6 months of the screening visit) the subject's clinical condition suggests to the investigator that their platelet count may have dropped, the subject may have their platelet count re-measured by the local laboratory. If the platelet count is  $\leq 20 \times 10^9/L$ , the general health of the subject has not significantly changed, and no changes in concomitant medications or treatment have occurred which would violate the inclusion criteria, then safety blood samples should be measured by the local laboratory e.g. CBC, LFTs, serum Creatinine/BUN. If these all meet the entry criteria then the subject can be considered as eligible, and can be immediately enrolled in the study.

*Other Blood Samples*

The following additional samples will be collected:

- Serum for IgG, IgA, and IgM levels
- A reserve sample (see Section 9.3.1)
- A sample for a Direct Coombs' test (see Section 9.3.2).
- NAT for HCV, HIV and Parvovirus B19
- Serology for HIV1 and HIV2, HCV, HBsAg
- Blood typing (A, B, O, Rh(D)+/-)

*Urinalysis*

A urinalysis with microscopic examination will be done as a part of this visit.

*Assessment for Bleeding/Hemorrhage*

The subject will be assessed for bleeding and hemorrhage; this will be graded as detailed in Appendix 1 and recorded on the subject's CRF.

*Concomitant medications*

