If the subject is enrolled within 14 days of screening, all medications the subject is taking at the time of screening may be continued through the completion of the second infusion, including corticosteroids; however, the dose must remain unaltered through Day 9 unless some condition of the subject requires a change. If possible, doses of corticosteroids or other immunosuppressant medications should remain constant until Day 32 (see Section 6.1). All concomitant medications will be recorded on the CRFs.

If the subject is not enrolled within 14 days of screening, it should be noted that doses/regimen of corticosteroid must have been stable for 2 weeks prior to Day 1; and doses/regimen of azathioprine, cyclophosphamide, and attenuated androgens must have been stable for 2 months prior to Day 1. Changes to the dosage of these medications should be avoided as mentioned above. In addition subjects are not to receive an IGIV preparation or an investigational agent or

any blood, blood product or blood derivative within 1 month prior to Day 1, and receipt of any live virus vaccine and Rituximab is not allowed within 3 months prior to Day 1.

Administration of corticosteroids to decrease adverse reactions to the infusion may not be given before the IGIV infusions. However, pre-medication with analgesic or antihistamine drugs is permissible if required.

No blood products, including IGIV (other than GAMMAPLEX in accordance with the protocol), may be given during the study until the End of Study visit (viral safety visit approximately 3 months after the last dose of GAMMAPLEX).

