## Bio Products Laboratory

## CONFIDENTIAL

- b) Vital Signs (blood pressure, heart rate, oral temperature, respiratory rate) should be taken as follows: 10 min before and at the start of each infusion, 10 min after initiation of each infusion, 10 min after each rate increase, 10 min and 30 min after maximum rate is achieved, every 60 minutes until infusion is complete, at the time the infusion stopped, and 15, and 30, after the infusion has stopped. Vital signs must be taken with the subject in the same position on each occasion.
- c) On Day 1 (and visit(s) to check platelet count, if applicable) only, a platelet count will also be done locally prior to infusion to confirm eligibility of the subject (2mL).
- d) For all subjects screened more than 14 days prior to Day 1, additional safety laboratory samples will be taken to be analyzed by the local laboratory e.g. CBC, LFTs, serum Creatinine/BUN.
- e) Laboratory A includes CBC with differential and platelet count.
- f) Laboratory B includes bilirubin, creatinine, BUN, ALT, AST.
- g) Director Coombs' Test - on Days 5 and 14, samples for LDH, haptoglobin, and urine hemosiderin will also be taken.
- h) NAT for HCV, HIV, and Parvovirus B19.
- i) Parvovirus B19 only will be tested on Day 9; 4-mL blood sample.
- j) Serology for HIV 1 & 2, HCV and HBsAg. **Note: If a positive result on an NAT or serologic test occurs, it will be repeated at the subject's next scheduled visit.**
- k) Immunoglobulins - IgG (all visits) and IgA and IgM (Screening and at End of Study visit only).
- l) The 1-mL sample needed for blood typing will come from the tube taken for the Direct Coombs' Test.
- m) For all subjects this visit will be approximately 3 months after the last dose of GAMMAPLEX and will be the End of Study visit for all subjects irrespective of whether they received 1, 2, or 3 courses. For subjects receiving 1 treatment course of GAMMAPLEX only, this visit will take place on Day 90.

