### 6.2. Exclusion Criteria

1. The subject has a history of any severe or anaphylactic reaction to blood or any blood-derived product, or any severe reaction to IGIV or any other IgG preparation.
2. The subject is known to be intolerant to any component of the investigational product.

3. The subject has received any live virus vaccine within the last 3 months.
4. The subject has received an IGIV preparation within 1 month prior to Day 1.
5. The subject is currently receiving, or has received, any investigational agent within the 1 month prior to Day 1.
6. The subject has received any blood, blood product, or blood derivative within the 1 month prior to Day 1.
7. The subject has received Rituximab within the 3 months before Day 1.
8. The subject is pregnant or is nursing.
9. The subject is positive for any of the following at screening:
  - HBsAg
  - NAT for HCV
  - NAT for HIV
  - Antibodies to HCV or HIV 1 or 2
10. The subject, at screening, has levels greater than 2.5 times the upper limit of normal, as defined by the central laboratory, of any of the following:
  - Alanine aminotransferase (ALT)
  - Aspartate aminotransferase (AST)
11. The subject has a severe renal impairment (defined as serum creatinine greater than 2 times the upper limit of normal or BUN greater than 2.5 times the upper limit of normal for the range of the laboratory doing the analysis); the subject is on dialysis; the subject has a history of acute renal failure.
12. The subject is known to have abused alcohol, opiates, psychotropic agents, or other chemicals or drugs within the past 12 months.
13. The subject has a history of deep vein thrombosis (DVT) or thrombotic complications of IGIV therapy
14. The subject has any history or sign of hyperviscosity, transient ischemic attack (TIA), stroke, other thromboembolic event, or unstable angina
15. The subject suffers from any acute or chronic medical conditions (e.g., renal disease or predisposing conditions for renal disease, coronary artery disease, or protein losing enteropathy) that, in the opinion of the investigator, may interfere with the conduct of the study
16. The subject has an acquired medical condition, such as chronic lymphocytic leukemia, lymphoma, multiple myeloma, chronic or recurrent neutropenia (defined as an absolute neutrophil count (ANC)  $< 1 \times 10^9/L$ ).
17. The subject has non-controlled arterial hypertension (systolic blood pressure  $>160$  mmHg and/or diastolic blood pressure  $>90$  mmHg).

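### End of Study IgG is compared with a screening value that can be 6 months old and is not covered by the IGIV washout, although a pre-infusion Day 1 IgG is already measured

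*Protocol*

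**What the plan says.** Section 9.3.1 fixes the reference: "IgG, IgA and IgM will be monitored at the End of Study visit and compared with the values obtained at screening". The same paragraph has IgG measured before infusion on Days 1 and 2 and at each follow-up visit to Day 32.

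On the timing of screening, Section 5.3.1.1 says "This visit can occur up to 6 months prior to Day 1", as does Section 5.3.

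The only IGIV washout is exclusion criterion 4 in Section 6.2: "The subject has received an IGIV preparation within 1 month prior to Day 1". Section 5.3.1.1 (Concomitant medications) repeats it for subjects enrolled more than 14 days after screening, again counted from Day 1. Earlier IGIV use is expected: "The medical history must include the use of previous IGIV treatments received".

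Table 1 marks a 5 mL immunoglobulin sample at both screening and Day 1. Its footnote k sets the assays: "Immunoglobulins - IgG (all visits) and IgA and IgM (Screening and at End of Study visit only". When screening is more than 14 days old, the local re-check gives blood count, liver tests and creatinine/BUN as its examples, and Table 1 marks no immunoglobulin sample at that visit.

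**The concern.** A change from baseline needs a reference that reflects the state just before treatment. The screening IgG need not. It may be months old, and nothing stops a subject from having received another IGIV product days before that sample, provided Day 1 falls more than a month after the product. Section 5.3.1.1 allows the necessary gap: a subject whose platelet count is above the limit at screening may be re-checked and enrolled at any time within 6 months.

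In such a subject, part of the screening IgG belongs to the earlier product. End of Study IgG can then appear to fall when it is in fact above the level just before GAMMAPLEX. The plan already holds a closer pre-dose IgG and does not name it as the reference.

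**Working it through.** **Is the Day 1 sample really drawn?** The Day 1 volumes in Table 1 are: local platelets 2, Laboratory A 2, Laboratory B 5, Coombs 2, NAT 13, serology 8, immunoglobulins 5, reserve 5, retention 2.5. They sum to 44.5 mL, the stated total. Without the immunoglobulin tube the sum would be 39.5 mL. The tube is drawn, and IgG is assayed on it.

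**Carry-over model.** The share of a dose's IgG increment remaining after t days is 2^(−t/h). Assumptions not in the documents: half-life h of 20 to 40 days, a prior dose equal to the study dose, stable endogenous IgG, one study course treated as given on Day 1, and one month taken as 30 days. From the protocol: at least 30 days from IGIV to Day 1, at most about 183 days from screening to Day 1, and End of Study 89 days after Day 1.

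| Days since dose | h = 20 | h = 40 |
|---|---|---|
| 7 | 0.7846 | 0.8858 |
| 16 | 0.5743 | 0.7579 |
| 30 | 0.3536 | 0.5946 |
| 89 | 0.0458 | 0.2139 |
| 119 | 0.0162 | 0.1272 |
| 190 | 0.0014 | 0.0372 |
| 279 | 0.0001 | 0.0079 |

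With h of 14 to 35 days instead, the shares are 71% to 87% at 7 days and 23% to 55% at 30 days.

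The cases below are in units of one dose increment, with h = 20 first and h = 40 second.

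**Case A: IGIV 7 days before screening, Day 1 183 days after screening.**
- End of Study minus screening: 0.0458 + 0.0001 − 0.7846 = −0.74; 0.2139 + 0.0079 − 0.8858 = −0.66.
- End of Study minus Day 1: 0.0458 + 0.0001 − 0.0014 = +0.04; 0.2139 + 0.0079 − 0.0372 = +0.18.
- The choice of reference reverses the sign.

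**Case B: IGIV 7 days before screening, Day 1 at the minimum washout (23 days after screening).**
- End of Study minus screening: 0.0458 + 0.0162 − 0.7846 = −0.72; 0.2139 + 0.1272 − 0.8858 = −0.54.
- End of Study minus Day 1: 0.0458 + 0.0162 − 0.3536 = −0.29; 0.2139 + 0.1272 − 0.5946 = −0.25.
- Day 1 is better, but still affected.

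**Case C: IGIV after screening, 30 days before Day 1.**
- The screening sample contains none of it.
- End of Study minus screening: 0.0458 + 0.0162 = +0.06; 0.2139 + 0.1272 = +0.34.
- End of Study minus Day 1: −0.29; −0.25, as in case B.
- Here Day 1 is the affected reference.

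**Subjects enrolled within 14 days of screening.** Any IGIV was at least 30 − 14 = 16 days before screening, so at most 57% to 76% remains at screening, against 35% to 59% on Day 1. The gap is smaller but has the same direction.

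**The case against.** The strongest objection is that Day 1 is not a clean baseline either. That stands: a 1-month washout can leave 35% to 59% of an equal prior dose under the same half-lives, and case C shows a permitted sequence in which Day 1 is the worse choice. A reader might infer that Day 1 gives the level free of earlier product. The documents do not support that.

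Second, the 7-day interval is a chosen unfavourable case, and the protocol gives no frequency for it. This also stands. The re-check route makes it possible, but nothing in the text shows it to be common.

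Third, a reader might extend the carry-over argument to IgA and IgM, since all three are compared in one sentence. The documents do not support this. The only IGIV composition given (Section 3.1) is virtually all IgG, with IgA below 10 µg/mL, and other products are not described. For IgA and IgM only the age of the reference is at issue, and screening is their only planned pre-treatment value.

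Fourth, the protocol never says that the comparison is meant to measure residual GAMMAPLEX, and the baseline for a descriptive laboratory summary is often left to the SAP. The first part is right. The second does not dispose of the point, because Section 9.3.1 itself names the screening value. The Day 1 IgG will exist, so the information is not lost; it is just not the stated reference.

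**Conclusion.** The point holds for IgG as a minor one. The stated reference can be up to 6 months old and has no washout of its own, while a closer pre-dose value is measured. If IGIV was given before screening and none between screening and Day 1, screening always carries more of it than Day 1, so End of Study minus screening is biased downward relative to the Day 1 comparison. In the 7-day example, 78% to 89% of the prior dose remains at screening, against at most 35% to 59% on Day 1. These figures rest on the assumed half-life of 20 to 40 days, an equal prior dose and a single study course. The number of subjects affected is unknown.

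It would be wrong to infer that Day 1 is always the better reference, or that any study conclusion is at risk. Immunoglobulins are not an efficacy variable (Sections 8.1 and 8.2), are not named among the safety analyses in Section 10.4, and enter no success rule. The effect is confined to a descriptive safety comparison.

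**What to change.** In Section 9.3.1, name the pre-infusion Day 1 value as the primary reference for End of Study IgG and keep the comparison with screening as supportive. Flag subjects who received IGIV shortly before screening or between screening and Day 1, so that both sequences can be read correctly. This needs a text change and use of the IGIV history and medication records; it needs no new blood, visit or assay.

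For IgA and IgM, keep screening as the reference and report how old it was at Day 1. Optionally, run both assays on the Day 1 immunoglobulin tube and amend footnote k of Table 1. That costs two assays per subject and no extra blood, but it adds tests and so may need regulatory and ethics approval under Section 14.1.
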